## Abstract

**Introduction:**

Maternal and child mortality has markedly decreased worldwide over the past few decades. Despite this success, the decline remains unequal across countries and is overall insufficient to meet the Sustainable Development Goals. South Asia and sub-Saharan Africa bear most of the burden of maternal and child morbidity and mortality. Major gaps persist in our understanding of the causes, timing, diagnostic thresholds and risk factors for adverse outcomes in these regions. Addressing these gaps requires new ways to prevent and treat disease, from novel diagnostics to precision public health strategies, all of which rely on high-quality clinical data from diverse populations. The Pregnancy Risk, Infant Surveillance, and Measurement Alliance (PRISMA) Maternal and Newborn Health Study aims to estimate population-level prevalence of morbidities and mortality and to assess biological, clinical and sociodemographic risk among mother–infant pairs in India, Pakistan, Kenya, Ghana and Zambia.

**Methods and analysis:**

This study is a prospective, open cohort study with a planned recruitment of about 6000 women annually across six research sites in five countries. Participants are pregnant women enrolled less than 20 weeks gestation, as determined by ultrasound, identified through active house-to-house and facility-based surveillance. Robust clinical data will be collected at 12 scheduled study visits during antenatal care, labour and delivery, and through 1 year postpartum. A total of 34 outcomes will be captured. The primary analysis will estimate the burden of adverse outcomes and examine associated risk factors to inform future intervention strategies. Data will also be used to develop normative values for pregnant and postpartum women, as well as predictive models to assess pregnancy risk.

**Ethics and dissemination:**

PRISMA received institutional and national ethical approvals. Findings will be published in peer-reviewed open-access journals and disseminated at national and international forums to inform clinical guidelines and public health practice.

**Trial registration number:**

NCT05904145.

STRENGTHS AND LIMITATIONS OF THIS STUDYHarmonised, multidimensional data collection on social, biological, clinical and environmental factors related to health and disease.Large, community-based sample of an estimated 18 000 pregnant women and 15 300 live births over the first 3 years of the study.Use of combined cutting-edge machine learning algorithms and predictive modelling approaches to better understand and predict risks.Morbidity and mortality estimates may not be fully generalisable to other settings.

## Introduction

Globally, the maternal mortality rate has declined by more than 43% since 1990.^1^ Despite this success, progress remains unequal between regions, with low-income and middle-income countries (LMICs) bearing excess burden.^2^ Southern Asia and sub-Saharan Africa account for 86% of all maternal deaths and have some of the world’s highest maternal mortality rates at 134 (80% uncertainty interval (UI) 118 to 155) and 545 (UI 477 to 654) per 100 000 live births, for each region, respectively.^3^ The WHO estimates that between 2003 and 2009 the top causes of death in both regions were haemorrhage, hypertensive disorders and sepsis.^4^ These three causes were responsible for over half of all maternal deaths. Indirect causes—such as HIV, malaria, tuberculosis, iron-deficiency anaemia or diabetes mellitus—accounted for another 27.5% of maternal deaths.^4^ However, due to challenges in event reporting and linking hospital records to national health surveillance systems, comprehensive data on the causes of maternal deaths and near-misses are lacking.^5–8^

Pregnancy-related and pre-existing conditions are a growing concern, not only given their potential to be life-threatening, but also due to the lasting effects they have on maternal and infant health and quality of life.^9 10^ It is well evidenced that maternal morbidities put women at risk of future complications and impact an estimated 4% to 8% of all deliveries.^11^ However, the true burden of maternal morbidities remains unclear, as these conditions frequently go undiagnosed or undocumented, most existing research focuses on a single sequela, and few large clinical cohorts have been conducted in LMICs. For example, a review of 59 studies (only four of which were conducted in Southeast Asia and sub-Saharan Africa) found that hypertensive disorders of pregnancy more than doubled the risk of ischaemic heart disease and heart failure later in life.^12^ Similarly, gestational diabetes and maternal anaemia have been identified as risk factors for long-term cardiovascular diseases.^13 14^ Another systematic review of 24 studies in high-income countries found that postpartum haemorrhage was linked to persistent physical, psychological and psychosocial problems, including mastitis, post-traumatic stress disorder, depression and delayed mother–infant bonding.^15^ The narrow clinical and geographical focus of available research limits our understanding of the full range of risks women face during and after pregnancy, and how this varies across health settings. Multidimensional research that assesses biological, clinical, demographic and social determinants of health is likely to improve risk prediction, thereby preventing maternal morbidities and reducing their enduring repercussions.

Infant health and development also suffer the consequences of maternal morbidities.^10 16^ Data from a WHO Global Survey of 172 461 singleton deliveries in 22 LMICs found that pre-eclampsia and pregestational diabetes significantly increased odds of provider-initiated and spontaneous preterm birth.^17^ Pre-eclampsia and gestational diabetes have been connected to heightened risk of lifelong adverse outcomes among offspring, including increased susceptibility to hypertension, kidney disease, nutritional deficiencies, cardiometabolic events, obesity, attention deficit hyperactivity disorder and autism spectrum disorder.^18–21^ Maternal infections and poor nutrition during pregnancy have been linked to suboptimal cognitive development for children.^22 23^ To provide newborns with the best start to a healthy life, improvements in antenatal care are essential to appropriately manage pre-existing conditions and screen for risk factors. Ultimately, addressing maternal morbidities not only benefits women’s health but further supports the long-term well-being of their children.

While early identification of morbidities and risk for adverse outcomes in the antenatal and postnatal periods is essential, correct diagnoses and risk prediction are hindered by the lack of empirical data underlying clinical guidance and risk stratification algorithms. Often these are predominantly derived from data collected among non-pregnant adults in limited geographies, most commonly the USA and China, due to concentrated investments in healthcare research and extensive electronic health systems.^24–27^ Data disparities limit the generalisability and predictive accuracy when applied to peripartum women.^25^ The rise of machine learning has further highlighted the issue, as generated predictive algorithms typically rely on datasets from high-income settings, restricting their applicability to LMICs.^24^ High-quality, representative data are required to inform clinical guidance and risk prediction tools for maternal morbidities; better data are needed to inform normative ranges for perinatal depressive symptoms, blood pressure, biomarkers for hypertensive disorders of pregnancy and haemoglobin levels.^28–30^ Addressing these evidence gaps by generating multidimensional global datasets for use in clinical benchmarking is critical to enabling accurate, equitable care for all women.

### Study rationale and objectives

Robust data on pregnancy risks—including medical history, clinical symptoms and diagnoses, behavioural and lifestyle factors, social and economic characteristics, environmental exposures and nutritional status—are essential to developing strategies to effectively manage pregnancy risks and improve outcomes in resource-constrained environments.^31 32^ Population-based, multidimensional, longitudinal data of mother–infant pairs is severely lacking, particularly from LMICs. This hinders our ability to estimate the prevalence of morbidities and mortality, and to attribute their various risk factors among pregnant women and infants during the antenatal and postnatal periods.^31^ We further lack the detailed, individual patient data needed to develop advanced diagnostic tools and risk prediction algorithms, as well as adequate baseline data needed to effectively monitor for adverse events in the context of introducing new devices, drugs and vaccines. Existing datasets have significant limitations in study designs or the completeness and accuracy of data collected. Often, data are self-reported, cross-sectional and most datasets are unable to be pooled in a harmonised way. These limitations make it difficult to achieve the robust datasets needed for analysis and for prioritising investments in research, development and policy or guideline changes.

We designed the Pregnancy Risk, Infant Surveillance, and Measurement Alliance (PRISMA) Maternal and Newborn Health Study in response to these critical gaps. At a high level, the study aims to evaluate pregnancy risk factors and their associations with adverse outcomes, including stillbirth, infant mortality and morbidity, and maternal mortality and morbidity. The resulting harmonised dataset will be used to estimate population-level disease and outcome burden in two South Asian and three sub-Saharan African countries, which will be evaluated to identify any overlooked health concerns in each study area. Our data will inform subsequent research to understand priority issues and to test innovative strategies that optimise pregnancy outcomes, including defining more representative and gestational-age-specific reference values for select biomarkers. The primary objectives are as follows: (1) To provide population-based prevalence estimates of key maternal and infant health outcomes, which may inform the development of future diagnostics and interventions; (2) To improve the global understanding of key risk factors for morbidity and mortality among pregnant women, their fetuses and mother–infant pairs for up to 1 year postpartum and (3) To collect data to enable the application of novel analytical techniques to create risk prediction tools.

## Methods and analysis

### Study design

The PRISMA Maternal and Newborn Health Study is an international, multisite, prospective, open-cohort study. Leveraging population-based and facility-based pregnancy surveillance systems, we will identify, screen and enrol pregnant participants prior to 20 weeks gestation as confirmed by ultrasound. Enrolment began in September 2022 in Pakistan, November 2022 in Kenya, December 2022 in Ghana and Zambia, June 2023 in South India and December 2023 in North India. Detailed clinical data will be collected to characterise the health status of women and their fetuses and infants, including ultrasound imaging, laboratory testing, physical examination, validated health surveys, medical history by maternal recall and facility record abstraction. Data collection will continue during the antepartum, intrapartum and postpartum periods up to 1 year following delivery. Participants will be assessed at scheduled visits at <20, 20, 28, 32 and 36 weeks gestation, at labour and delivery, at 3 days postpartum, and 1, 4, 6, 26 and 52 weeks postpartum. Liveborn infants will be similarly assessed at birth, day three of life, and 1, 4, 6, 26 and 52 weeks old. Any additional visits or hospitalisations, for example, due to complications, will also be documented. In the event of a miscarriage or stillbirth, participants will be followed up through 6 weeks and 1 year, respectively. Verbal autopsies will be conducted in the case of maternal, fetal, neonatal or infant death and analysed by InterVA computer software to ensure a harmonised approach to cause of death determination. The study protocol will be implemented uniformly across sites to ensure that all laboratory and diagnostics tests, primary health outcomes and related risk factors are measured correctly and consistently.

### Study outcomes

We aim to capture data on 34 adverse health outcomes (table 1), which are defined in online supplemental file. Outcomes were selected based on high-priority research gaps within study contexts and determined via an interactive protocol development process with input from study investigators and other subject matter experts. Feasibility was also considered when selecting the measurement method. Clinical definitions, measurements and constructed variables for each health outcome are standardised across study sites.

10.1136/bmjopen-2025-104512.supp1Supplementary data

**Table 1 T1:** Study outcomes by population and level

Outcome level	Population	
	Gravida/puerperium	Fetus/infant
Primary	1. Maternal mortality 2. Composite severe maternal outcomes 3. Maternal anaemia	4. Stillbirth 5. Neonatal mortality 6. Low birth weight 7. Preterm birth 8. Small-for-gestational-age
Secondary	9. Late maternal mortality 10. Pre-eclampsia 11. Gestational hypertension 12. Postpartum hypertension 13. Medical indication for preterm delivery 14. Preterm premature rupture of membranes 15. Gestational diabetes 16. Maternal infection and sepsis 17. Perinatal depression	18. Fetal death 19. Infant mortality 20. Cause of neonatal mortality 21. Timing of neonatal mortality 22. Cause of stillbirth 23. Timing of stillbirth 24. Hyperbilirubinaemia 25. Neonatal sepsis 26. Possible severe bacterial infection 27. Postnatal weight trajectory 28. Infant growth
Tertiary	29. Placental disorders 30. Uterine rupture 31. Prolonged labour 32. Unplanned surgery 33. Antepartum and postpartum haemorrhage	34. Perinatal birth asphyxia

### Study settings

Data collection will occur in six study areas: Kisumu and Siaya, Kenya; Kintampo, Ghana; Lusaka, Zambia; Vellore, India; Hodal, India; and Rehri Goth and Ibrahim Hyderi, Karachi, Pakistan. Protocol implementation is jointly carried out by clinical teams at participating health facilities and study staff from partnering research institutions (ie, the Kenya Medical Research Institute, Kintampo Health Research Centre, University of North Carolina Global Projects Zambia, Christian Medical College Vellore, Society for Applied Studies and Aga Khan University). Clinical assessments and subsequent findings conducted by study staff will be integrated with clinical care. Researchers at the George Washington University are responsible for protocol harmonisation and central data coordination. Consortium institutions and investigators were appointed by the Gates Foundation based on existing research infrastructure and expertise. Each country team identified and mapped geographical areas in which to conduct the study. Estimates of the study area population size are described in table 2.

**Table 2 T2:** Estimates of study area population size, pregnancies and live births

Study area	No. households	No. women of reproductive age	Total population size	Anticipated no. pregnancies (live births)*
Kintampo, Ghana	34 640	45 767	177 200	3000 (2250)
Vellore, India	54 435	47 443	234 624	2700 (2300)
Hodal, India	36 321	35 499	196 678	2000 (1700)
Kisumu, Kenya	44 932	47 826	171 698	3000 (2550)
Karachi, Pakistan	23 170	34 682	227 549	6000 (5100)
Lusaka, Zambia	31 165	34 942	145 263	2250 (1914)
All sites	224 663	246 159	1 153 012	18 550 (15 814)

*Anticipated number of pregnancies based off expected annual enrolment over 3 years; expected 85% of pregnancies to result in a live birth.

### Eligibility criteria

Women who meet the following criteria may be eligible for enrolment: lives within the study catchment area with no plans to permanently relocate during pregnancy or within 1 year postpartum; meets minimum age requirement for consenting in country of residence (Ghana: 15 years of age; Kenya: 18 years of age or emancipated minors; Pakistan: 15 years of age or emancipated minors; Zambia: 15 years of age; India: 18 years of age) and viable intrauterine pregnancy less than 20 weeks gestation determined by ultrasound. Women who have more than one pregnancy during the study period are eligible for re-enrolment. Multiple gestations (ie, two, three or more fetuses) will also be eligible.

### Pregnancy surveillance

Household-based and facility-based surveillance systems will be used to identify women of reproductive age with suspected pregnancies. Routine health and demographic surveillance systems, either existing or established for the purpose of this study, will be leveraged to visit homes in the study catchment area at least once every 6 months. Women identified at these visits will be invited to provide basic socio-demographic information as a part of the population-based surveillance and screened for study eligibility. Women who receive antenatal care at participating health facilities will also be identified and screened. Combined, these women make up the sampling frame for the study cohort.

### Participant identification and enrollment

A multiphase process of prescreening, consenting and screening will be used to enrol participants (figure 1). Identified women of reproductive age will be prescreened for potential eligibility by community fieldworkers based on the following criteria: reported symptoms or clinical signs of pregnancy; estimated gestational age per last menstrual period <25 weeks; lives within the study catchment area; and meets minimum age requirement in each study site. Any woman potentially eligible after prescreening will be invited to provide informed consent or assent in her preferred language. Certified sonographers will then conduct an ultrasound to verify that the woman has an intrauterine pregnancy and is prior to 20 weeks gestation. Women who are beyond the gestational age threshold or with a non-viable pregnancy (eg, ectopic) are not eligible to participate and will be referred.

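### The prescreen requires gestation under 25 weeks by last menstrual period before the scan, so as written it excludes women who conceive before menses return after a birth, although they are eligible by ultrasound

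*Protocol article*

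**What the plan says.** The section on eligibility criteria in the protocol article sets the gestational-age requirement by scan: "viable intrauterine pregnancy less than 20 weeks gestation determined by ultrasound". LMP is not an eligibility criterion there. The same section adds: "Women who have more than one pregnancy during the study period are eligible for re-enrolment".

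The section on participant identification and enrolment describes the steps in order:

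1. Prescreening: "Identified women of reproductive age will be prescreened for potential eligibility by community fieldworkers based on the following criteria". Four criteria follow and must be met together: signs or symptoms of pregnancy, "estimated gestational age per last menstrual period <25 weeks", residence in the catchment, and minimum age.
2. Consent: "Any woman potentially eligible after prescreening will be invited to provide informed consent or assent in her preferred language".
3. Scan: "Certified sonographers will then conduct an ultrasound to verify that the woman has an intrauterine pregnancy and is prior to 20 weeks gestation".

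The pregnancy surveillance section gives a second way of being identified: "Women who receive antenatal care at participating health facilities will also be identified and screened". It states no separate gestational-age rule for that route. The article names no alternative for an LMP that is unknown or that predates a previous birth. Figure 1, which shows the identification flow, is not available in the text at hand.

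**The concern.** The less reliable dating method comes before the decisive one and can overrule it. The five weeks between the 20-week limit and the 25-week prescreen allow for ordinary error in recalled dates. They cannot absorb the case where the last period belongs to the cycle before an earlier pregnancy.

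The women affected are within the intended population. Re-enrolment is expressly allowed, participants are followed to 52 weeks postpartum, and some conceptions in that year will precede the return of menses. The same applies to women with a recent birth who were never enrolled before.

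The first primary objective is "To provide population-based prevalence estimates of key maternal and infant health outcomes", and the second concerns risk factors. A rule that removes pregnancies because they follow closely on a birth selects on a characteristic that an analyst may want to study as an exposure. The loss occurs before enrolment, so no analysis of the cohort can recover it. Where the criterion cannot be evaluated, sites may also settle the matter differently, although the article promises uniform implementation.

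**Working it through.** The plan gives no figure of its own to reproduce. The check is whether an eligible woman can fail the LMP criterion.

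**Inputs from the document.** LMP limit 25 weeks (participant identification and enrolment); ultrasound limit 20 weeks (eligibility criteria).

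**Inputs assumed.** B, gestation at the previous birth: 20 to 40 weeks. w, weeks from that birth to the new conception: 3 to 26. g, true gestation of the new pregnancy at prescreening: 5 to 19 weeks.

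**1. Conception before menses return.** If the last period preceded the previous pregnancy,

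LMP gestation = B + w + (g − 2),

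where 2 weeks are subtracted because gestation is counted from two weeks before conception.

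| B | w | g = 5 | g = 19 |
|---|---|---|---|
| 20 | 3 | 26 | 40 |
| 20 | 26 | 49 | 63 |
| 28 | 3 | 34 | 48 |
| 28 | 26 | 57 | 71 |
| 40 | 3 | 46 | 60 |
| 40 | 26 | 69 | 83 |

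The range is 26 to 83 weeks. After a birth at 40 weeks the minimum is 40 + 3 + 5 − 2 = 46. No combination falls below 25, although every woman in the table is truly under 20 weeks.

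**2. Women with a usable LMP.** The criterion wrongly rejects an eligible woman only if her LMP overstates gestation by at least 25 − g weeks. That is 15 weeks at a true gestation of 10, and just over 5 weeks when she is just under 20. For ordinary recall error the margin is reasonable, so the defect is specific to the amenorrhoea case.

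**3. Unknown LMP.** Nothing can be computed. The criterion has no value, and the text gives no default in either direction.

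**4. Second chance.** Households are visited at least once every 6 months, about 26 weeks. At that minimum frequency, a woman rejected at a true gestation of 5 weeks would next be seen at about 5 + 26 = 31 weeks, past the ultrasound limit.

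**5. Effect on prevalence, illustration only.** Let f be the share of the target population rejected and RR their risk relative to the other women. Then

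true prevalence / cohort prevalence = 1 + f(RR − 1).

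The document gives neither f nor RR. If f were 3% to 10% and RR were 1.5, the ratio would be 1.015 to 1.05. On a cohort prevalence of 15%, also assumed, that is 0.225 to 0.75 percentage points. With RR = 1 there is no bias, and with RR below 1 the direction reverses.

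**The case against.** The strongest reply is that the prescreen is only field triage. Final eligibility is by ultrasound, and the prescreen passes on anyone who may be eligible. A fieldworker who obtained 50 weeks or more would see that this cannot describe a current pregnancy. Returning participants have postnatal visits at 4, 6, 26 and 52 weeks, so study staff would know when they last delivered. Antenatal attenders are identified separately, and how the fieldworker prescreen applies to them is unclear. Handling of an unusable LMP is also the kind of detail that an article leaves to a form or operating procedure, and Figure 1 is not shown.

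Much of this limits the claim. Total exclusion in practice is not established, and an unseen procedure may already contain an exception. A reader might infer that women with no LMP are rejected. The article does not say so: it is silent, and sending them to the scan fits its wording equally well. A reader might also infer that prevalence is biased downwards, or try to count the women lost. Neither is supported. The direction depends on risks the document does not give, and the pregnancy numbers in Table 2 rest on expected enrolment, so a share of all catchment conceptions cannot be applied to them.

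The reply does not remove the core point. The article does more than omit a detail: it states a criterion that must be met before consent and scan, and that criterion rejects women whom its own eligibility section admits. Relying on a fieldworker to recognise an implausible figure is relying on departure from the rule as written.

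**Conclusion.** The point holds for women who conceive before menses return after a birth. Applied as written, the LMP criterion excludes them at every combination of timings examined, with an LMP gestation of at least about 46 weeks after a term birth. This rests on two premises: that the last actual menses is the date used, and that the assumed ranges for gestation at birth and interval to conception are wide enough. It does not extend to conception after an early loss, where the last period may be more recent.

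For an unknown LMP the finding is narrower: the criterion cannot be evaluated and no route to the scan is stated.

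The consequence is selective removal of very short interpregnancy intervals from a cohort intended to be population-based. How many women are affected, and how far and in which direction any estimate moves, cannot be derived from the document. The percentages under step 5 of the working show how the bias would scale and are not estimates. The rule should be changed, because the loss cannot be repaired in analysis and the correction is small. If an operating procedure already provides the exception, only the article's description needs correcting.

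**What to change.** Reword the prescreen criterion to: LMP gestation under 25 weeks, or LMP unknown, or LMP earlier than the most recent birth. Let the ultrasound already in the plan decide eligibility, and apply the same wording to women identified at facilities. Do not add an exception for pregnancies that look advanced, since that would give fieldworkers at six sites an undefined judgement to make.

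Record on the prescreening form which of the three conditions was met, so that the number of women admitted by the new wording can be reported. Report by site how many women were rejected on the LMP criterion before the change.

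The cost is a one-line change to the form and procedure, plus some additional screening scans in women who prove to be 20 weeks or more. Enrolment began between September 2022 and December 2023, so the prescreen would change part-way through an open cohort. The date of the change at each site should be recorded and reported.
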